### Sample size

As this is a feasibility trial, a formal sample size calculation is not appropriate. On a pragmatic basis, a total of 90 participants (30 participants per treatment arm) has been deemed sufficient to estimate each component of the primary outcome, including recruitment rate, retention and acceptability and adherence in the intervention arms. Specifically, the overall retention rate has an estimated 95% CI of approximately ±10%, and acceptability and adherence within each treatment arm will have an estimated interval of approximately ±20%.

Recruitment will be monitored closely to ensure adequate participant enrolment to meet the target sample size. In the event of recruitment challenges, the TSC will advise on appropriate strategies to improve recruitment, for example, by revising the eligibility criteria or implementing targeted recruitment campaigns.

### Statistical methods

All analyses will follow the intention-to-treat principle. As this is a feasibility trial, the study is not powered to detect differences in outcomes between groups. The primary focus of the analysis will be on estimation to inform the design of a future pragmatic effectiveness trial. Appropriate descriptive statistics will be used to summarise quantitative data, both overall and by treatment arm (eg, means and SD for continuous variables, frequencies and percentages for categorical variables). At each postrandomisation timepoint, each clinical outcome for each treatment group will be summarised using suitable descriptive statistics. No subgroup analyses are planned.

To explore the potential effects of the allocated treatment on clinical outcomes, linear mixed-effects regression models will be used. Each model will include a random intercept to account for repeated measures within participants, with fixed effects for treatment group, time (as a categorical variable) and their interaction to estimate between-group differences at each timepoint. Adjusted mean differences between groups will be reported, along with 80% and 95% CIs.

Loss to follow-up will be reported by treatment arm and assessment timepoint. Missing data will be summarised using descriptive statistics. The primary analysis will use all available data without imputation, under the assumption that data is missing at random. The extent and pattern of missingness will be examined to inform the design of a future trial.

Sensitivity analyses, including per-protocol analyses, may be conducted where appropriate to explore the impact of adherence and protocol deviations. In accordance with the Consolidated Standards of Reporting Trials (CONSORT) extension for pilot and feasibility studies, no formal hypothesis testing will be undertaken and p values will not be reported.^33^

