Emerging evidence indicates that durable disease control may be achievable through strategies that reduce biologic exposure. Several studies have shown that disease control can often be maintained for extended periods following biologic discontinuation and is typically regained quickly on retreatment, without major safety concerns.^413^,^17^ A recent systematic review reported median times to relapse ranging from 12 to 34 weeks following biologic discontinuation, with longer periods of disease control observed after cessation of IL-23 inhibitors.^18^ Notably, in most studies, biologic discontinuation occurred relatively early in the treatment course (typically between 12 and 28 weeks), shortly after disease control was achieved.^1315^,^17^ This raises the possibility that maintaining disease control for a longer duration prior to discontinuation may lead to even more favourable outcomes.

To date, most biologic dose minimisation studies in psoriasis have employed standardised, stepwise dose reduction protocols, applying the same tapering schedule across all participants.^19 20^ While structured, this ‘one-size-fits-all’ approach does not account for individual variation. As healthcare models seek to become increasingly personalised, there is a need for more flexible, individualised strategies. One such approach involves adjusting the biologic dosing interval based on individual response, so further doses are only given if disease control is no longer maintained.^21^ As self-reported skin status is a reliable method for monitoring psoriasis,^22^ patients are well positioned to detect disease recurrence themselves through the appearance of a skin plaque. This opens the possibility of a patient-led ‘as-needed’ approach, in which biologic treatment is paused and restarted by the patient at the first sign of recurrence.^23^ This strategy may enhance patient empowerment and reduce treatment burden; however, its safety and effectiveness in real-world clinical settings remain untested.

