### Objectives

The primary objective of this study is to determine the practicality and acceptability, to both patients and clinicians, of two personalised biologic dose minimisation strategies compared with continuous treatment in adults with chronic plaque psoriasis who have been clear or nearly clear for ≥12 months on risankizumab monotherapy. The treatment strategies are:

Patient-led ‘as-needed’ treatment: risankizumab is self-administered at the first self-assessed sign of psoriasis recurrence, supporting patient empowerment and self-management.^23^TDM-guided treatment: a PK model-informed precision dosing approach is used to generate a personalised dosing interval (via an online dashboard), based on serum risankizumab concentration and individual covariates.^27^Continuous treatment: ongoing fixed interval risankizumab dosing, as per standard care.

The secondary objectives are to:

Provide preliminary data on the potential clinical effectiveness, safety, tolerability and treatment burden of (1) patient-led ‘as-needed’ treatment and (2) TDM-guided treatment compared with (3) standard care (continuous treatment). These data will allow estimation of effect sizes to inform sample size calculations for a future definitive trial.Assess the feasibility of collecting data on healthcare costs and resource use for each treatment strategy.Refine the model-informed precision dosing dashboard for TDM-guided risankizumab dosing using longitudinal PK data and pharmacodynamic (PD) data, to enhance its future utility.^27^

The exploratory objectives are to:

Determine the feasibility of self-sampling blood, which may be used in future research and clinical care.Determine the feasibility of genotype testing, which may be used in future research and clinical care.

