### Participants and recruitment

Participants are eligible for the trial if they meet the inclusion and exclusion criteria outlined in table 1. Figure 2 summarises the flow of participants through the study.

**Table 1 T1:** Eligibility criteria

Inclusion criteria	Exclusion criteria
Adults aged ≥16 years with a diagnosis of chronic plaque psoriasis with evidence of clear or nearly clear skin on risankizumab monotherapy for ≥12 months. Physician Global Assessment of clear or nearly clear skin at study entry. Clinician assessed Psoriasis Area and Severity Index ≤2 at study entry. Patient Global Assessment of clear or nearly clear skin at study entry.	Receiving risankizumab for a primary indication other than psoriasis. Concomitant immune-modifying therapy or phototherapy.

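### The random-intercept model imposes one variance on every visit and arm, so its visit-specific confidence intervals may be wrong in either direction

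*Protocol article*

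**What the plan says.** Statistical methods specifies linear mixed-effects models for the clinical outcomes. On the within-participant structure it says only: "Each model will include a random intercept to account for repeated measures within participants". The mean structure is set out "with fixed effects for treatment group, time (as a categorical variable) and their interaction to estimate between-group differences at each timepoint", and the output is fixed: "Adjusted mean differences between groups will be reported, along with 80% and 95% CIs". No hypothesis tests or p values are planned. The same section plans descriptive summaries of each clinical outcome by arm at each post-randomisation timepoint, with means and SDs as the example.

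Table 1 restricts the outcome scales at entry: "Clinician assessed Psoriasis Area and Severity Index ≤2 at study entry" and "Patient Global Assessment of clear or nearly clear skin at study entry", with a matching limit on the Physician Global Assessment. In Table 2, patient-reported outcomes are collected at months 3, 6, 9 and 12. PASI and Physician Global Assessment have no scheduled follow-up assessment before month 12.

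One arm pauses treatment and restarts on recurrence, one follows a model-derived dosing interval, and one stays on fixed dosing. The Background cites "median times to relapse ranging from 12 to 34 weeks following biologic discontinuation" and, in the same paragraph, says that control usually returns quickly on retreatment. Under Objectives, the secondary-outcome data have a stated use: "These data will allow estimation of effect sizes to inform sample size calculations for a future definitive trial".

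**The concern.** A random intercept with constant residual variance assumes equal variance at all visits, equal correlation between all pairs of visits, and the same variance in all arms. The design gives reason to doubt this. Entry criteria compress PASI and the global assessments at baseline. Afterwards two arms reduce exposure and the comparator does not, so spread can change over time and differ between arms.

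The trial is about estimation, so the visit-specific intervals are the main product of these models. If the variance is averaged over visits and arms with unequal spread, the interval at a given visit does not have its stated coverage. Readers planning the definitive trial would then misjudge the precision of the effect estimates.

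**Working it through.** **Inputs.** 30 participants per arm (Sample size). Visits as in Table 2. PASI lies between 0 and 2 at entry, so its baseline SD can be at most about 1 (half the range). The documents give no SD by visit; all SD profiles below are assumptions, in relative units.

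**The plan's own precision figures.** These concern proportions, not the mixed models. 1.96 × √(0.5 × 0.5/90) = 10.3 points and 1.96 × √(0.5 × 0.5/30) = 17.9 points, in line with the stated ±10% and ±20%. No figure is stated for the mixed-model intervals.

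**Formula.** With complete data and a full group-by-time interaction, the random-intercept model gives SE² = 2V/n at every visit, where V is the residual variance averaged over all modelled arms and visits. The true SE² for arms j and k at visit t is (v_jt + v_kt)/n. Hence

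- R = model SE / true SE = √{V / [(v_jt + v_kt)/2]}
- actual coverage = 2Φ(zR) − 1, with z = 1.960 or 1.282.

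**Worked case, months 3 to 12, SD doubling linearly.** SDs 1, 1.33, 1.67, 2; variances 1, 1.78, 2.78, 4.

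- All arms: V = 9.56/4 = 2.39. Month 12: R = √(2.39/4) = 0.77, coverage 87% and 68%. Month 3: R = √2.39 = 1.55, so too wide. A 5,000-run simulation gave 86.3% and 67.6% at month 12.
- Minimisation arms only, against continuous: V = (2 × 2.39 + 1)/3 = 1.93; true value (4 + 1)/2 = 2.5; R = 0.88; coverage 91.5% and 74%. Simulation gave 91.5% and 74.8%.

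**Other shapes, month 12.**

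| Assumed SD profile | R | 95% CI covers | 80% CI covers |
|---|---|---|---|
| Baseline to month 12: 1, 1.5, 2, 2.5, 3, all arms | 0.71 | 83% | 63% |
| Same rise, minimisation arms only, v continuous | 0.82 | 89% | 70% |
| 1 at baseline, then 2 throughout, all arms | 0.92 | 93% | 76% |
| Same plateau, minimisation arms only, v continuous | 1.02 | 95% | 81% |
| Peak: 1, 2, 3, 2.5, 2, minimisation arms only, v continuous | 1.19 | 98% | 87% |

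In the peak profile the month-6 interval is the one that is too narrow (R = 0.84, 90%).

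**Relapse and retreatment simulation.** This used relapse medians of 12, 20 and 34 weeks, assumed recovery times of 4–12 or 8–16 weeks, and assumed that the drug-monitoring arm behaves like the as-needed arm. Month-12 coverage of the 95% interval was 94.9% to 95.6%. With baseline left out of the modelled outcomes, R was 1.05 to 1.13 at months 3 to 12, so slightly too wide.

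**PASI and Physician Global Assessment.** If baseline is modelled as an outcome alongside month 12, with the SD going from 1 to 2:

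- All arms: V = (1 + 4)/2 = 2.5; R = √(2.5/4) = 0.79; coverage 88% and 69%.
- Minimisation arms only: V = (2.5 + 2.5 + 1)/3 = 2. Against continuous, R = √(2/2.5) = 0.89; coverage 92% and 75%. Between the two minimisation arms, R = √(2/4) = 0.71; coverage 83% and 64%.

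**Is a common unstructured covariance enough?** No. If the month-12 variances are 4, 4 and 1, it pools them to 3, while minimisation against continuous needs 2.5. √(3/2.5) = 1.10, an SE about 10% too large.

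**The case against.** A reader might infer that the month-12 intervals will be too narrow, the early ones too wide, and the definitive trial therefore too small. The documents do not support that.

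- **Direction.** It requires spread to keep rising to month 12. No SD by visit is given. The cited relapse times refer to stopping treatment, and the same paragraph reports quick recovery on retreatment. The as-needed arm restarts once the patient's own rating reaches mild, and the drug-monitoring arm is not a discontinuation arm. A plateau or mid-trial peak is at least as plausible, and month-12 coverage is then near or above nominal.
- **Scope.** PASI has no scheduled assessment at months 3, 6 or 9, so growth between those visits says nothing about it. The PASI problem arises only if baseline is modelled as an outcome, which the article does not say. Of the outcomes collected every three months, only the Patient Global Assessment is restricted at entry.
- **Sample size.** Under the doubling scenario, pooled over month-12 variance is 2.39/4 = 0.60, which suggests a trial at 60% of the needed size. But unpooled SDs by arm and timepoint are already planned, and nothing says the model's pooled variance would be used.
- **Level of detail.** Residual covariance and robust standard errors are often left to the analysis plan, which is not shown, and these are exploratory analyses without tests.

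The first three objections stand and limit the point. The fourth only softens it: the article does state a model, and that model as worded has one within-participant term.

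**Conclusion.** The point holds in limited form. As stated, the model forces one variance on all visits and arms, and the entry restrictions and contrasting dosing strategies make that doubtful. The resulting intervals may be too narrow or too wide, depending on where the spread is greatest.

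Under an assumed doubling of the SD over months 3 to 12, the nominal 95% interval at month 12 covers about 87% (all arms) or about 92% (minimisation arms only, against continuous). The plateau, peak and relapse-and-retreatment profiles give 93% to 98%. For PASI and Physician Global Assessment, if baseline is an outcome row, the month-12 interval is too narrow when spread grows in all arms or in both minimisation arms: about 88% for a doubling in all arms.

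These figures rest on complete data, 30 per arm, constant residual variance in the fitted model and assumed SD profiles. Neither a definite direction at month 12 nor an undersized definitive trial is shown. The consequence is moderate: no test or progression rule depends on these intervals, but they are the main output of the clinical models and bear on the next trial's design.

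**What to change.** 1. **Outcomes at months 3, 6, 9 and 12.** Keep the fixed effects. Replace the random intercept with an unstructured within-participant covariance, fitted by REML with Kenward-Roger degrees of freedom. Let spread differ by arm through arm-specific variances or robust standard errors; if the robust route is taken, use a small-sample correction. If the model does not converge, use a heterogeneous-variance structure.
2. **PASI and Physician Global Assessment.** Use a month-12 regression adjusted for baseline, with robust standard errors. Baseline then does not enter the outcome variance.
3. **Planning the definitive trial.** State that its SDs come from the visit- and arm-specific descriptive statistics already planned, not from the model's pooled variance.

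**Cost.** This changes wording only and uses standard software. A common unstructured covariance over four visits has 10 parameters against 2, so eight more; arm-specific variances add further terms. If equal variance is in fact true, intervals widen by about 1%. For example, with within-person correlation 0.5 the random-intercept contrast has 1/(0.625²/87 + 0.375²/261) ≈ 199 degrees of freedom (t = 1.972), against 87 for the unstructured model (t = 1.988), and 1.988/1.972 = 1.008. There is a small chance of non-convergence, which the fallback covers.

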### Randomisation and blinding

Participants will be randomised (1:1:1 ratio) to one of three treatment strategies: (1) patient-led ‘as-needed’ treatment, (2) TDM-guided treatment and (3) continuous treatment (standard care). Randomisation will be conducted via a secure online system to ensure allocation concealment. Stratification will be based on recruiting site and clear or nearly clear skin status, with randomly varying block sizes used to maintain allocation concealment and achieve balanced group sizes across these categories.

Although participants and the research team will not be blinded to the treatment strategy allocated, disease severity assessments, including the Psoriasis Area and Severity Index (PASI) and Physician Global Assessment, will be conducted by an assessor who is blinded to treatment allocation and is not involved in the participant’s care. Participants will be asked not to reveal their allocated treatment strategy to this blinded assessor. The blinded assessor will be either a dermatologist or a dermatology nurse.

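### The mixed model promises adjusted differences but lists neither randomisation stratum nor the baseline outcome, so the exploratory intervals may be wider than they need be

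*Protocol article*

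**What the plan says.** Randomisation and blinding: "Stratification will be based on recruiting site and clear or nearly clear skin status". Allocation is 1:1:1, with 30 participants planned per arm.

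Statistical methods sets out the comparative model for the clinical outcomes. On the random part it says: "Each model will include a random intercept to account for repeated measures within participants". The other terms of the model are then listed: "with fixed effects for treatment group, time (as a categorical variable) and their interaction to estimate between-group differences at each timepoint". The next sentence reads: "Adjusted mean differences between groups will be reported, along with 80% and 95% CIs". No adjustment variable is named there or elsewhere in the article, and the text does not say whether baseline counts as one of the time levels.

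The same section makes estimation the main aim and rules out p values. Objectives says that the secondary clinical data are meant to supply effect sizes for sizing the definitive trial.

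**The concern.** Two things do not fit together.

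First, the differences are labelled adjusted, but the listed terms contain nothing prognostic to adjust for. Arm, time and their interaction reproduce the group means at each time. The random intercept does not supply baseline adjustment either. With complete data and free means for every arm and time, the estimated difference at a follow-up time is simply the raw difference in means, even if baseline is one of the time levels. Chance baseline differences between arms of 30 therefore carry straight through.

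Second, the design balances the arms on site and skin status, but the model does not use that balance. Stratified allocation removes between-stratum variation from the true sampling error of the contrast. A model without the strata leaves that variation in the residual, so its standard error is too large.

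The two omissions act differently. Leaving out the strata makes intervals conservative (coverage above nominal). Leaving out the baseline keeps coverage correct but gives up precision. At stake is the precision of the estimates that the definitive trial would be planned from.

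**Working it through.** **The plan's own figures.** Sample size gives "the overall retention rate has an estimated 95% CI of approximately ±10" per cent for retention, and "acceptability and adherence within each treatment arm will have an estimated interval of approximately ±20" per cent. With p = 0.5, 1.960 × √(0.25/90) = 0.103 and 1.960 × √(0.25/30) = 0.179 (Clopper–Pearson 0.107 and 0.187). Both agree with the rounded statements. They concern the feasibility proportions, which this point does not affect. The plan states no width for the mixed-model differences, so the rest is in SD units.

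**No covariates, one timepoint, 30 v 30.** SE = √(2/30) = 0.258 SD. Half-widths are 1.960 × 0.258 = 0.506 (95%) and 1.282 × 0.258 = 0.331 (80%).

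**Baseline as covariate.** Multiply by √(1 − ρ²), where ρ is the baseline to follow-up correlation (assumed; not in the document).

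| ρ | factor | 95% half-width | 80% half-width |
|---|---|---|---|
| 0.2 | 0.980 | 0.496 | 0.324 |
| 0.3 | 0.954 | 0.483 | 0.316 |
| 0.5 | 0.866 | 0.438 | 0.287 |
| 0.6 | 0.800 | 0.405 | 0.265 |
| 0.7 | 0.714 | 0.361 | 0.236 |

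**Baseline and strata together.** This was simulated with 1,500 trials per setting, 90 participants, three arms, and permuted blocks of 3 or 6 within site by skin status. One timepoint was analysed, with sites as fixed terms. Assumed: 60% clear at entry, 5, 10 or 15 sites, and baseline independent of the strata. The table gives the 95% width as a ratio to the model without covariates.

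| ρ; site ICC; share of variance from skin status | 5 sites | 10 sites | 15 sites |
|---|---|---|---|
| 0; 0; 0 | 1.010 | 1.023 | 1.046 |
| 0.2; 0.02; 0.02 | 0.970 | 0.982 | 1.007 |
| 0.3; 0.05; 0.05 | 0.914 | 0.926 | 0.943 |
| 0.5; 0.05; 0.05 | 0.818 | 0.826 | 0.843 |
| 0.6; 0.10; 0.05 | 0.711 | 0.720 | 0.733 |

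Hand check of the last row: √(1 − 0.36 − 0.10 − 0.05) = 0.70, against 0.711 with 5 sites. With 15 sites there are 30 strata and on average 90/30 = 3 participants in each. Many blocks are then incomplete and the site terms cost degrees of freedom, which is why weak covariates bring no gain there.

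**Coverage.** In the nine settings with site ICC and skin-status share of at least 0.05:

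| Model | nominal 95% | nominal 80% |
|---|---|---|
| As written (no covariates) | 95.7–96.7% | 81.5–83.7% |
| Baseline added, strata omitted | 94.9–97.1% | 81.5–85.7% |
| Strata added | 94.1–96.2% | 79.3–81.4% |
| Both added | 93.9–95.5% | 79.5–81.7% |

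The simulation error is √(0.95 × 0.05/1500) = 0.6 points for 95% and √(0.8 × 0.2/1500) = 1.0 point for 80%. The excess for the model as written is therefore small, but it has the same sign in all nine settings.

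**Which outcomes have a usable baseline.** Table 2 schedules PASI, Physician Global Assessment and Patient Global Assessment at screening and at the baseline visit. DLQI, EQ-5D-5L, itch, PHQ, GAD, BIPQ and PsAID first appear in the Training column, and Interventions places training after randomisation. Weeks in disease control and worsening episodes have no baseline value.

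**The case against.** The strongest reply is that the article says what each model will include, not that it includes nothing else. The word adjusted may point to covariates listed in an analysis plan that is not shown. That is possible, so a reader should not infer that the trial team has decided against adjustment. But the protocol does fix a list of terms, and an analysis plan that followed it would omit the strata. The list and the label disagree on the page, and that remains to be settled.

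A reader might also infer that the intervals are a fifth to a third too wide. That follows only if strata explain 10–20% of variance and ρ is 0.5–0.6: √(1 − 0.10 − 0.25) = 0.81 and √(1 − 0.20 − 0.36) = 0.66. Nothing in the document supports those values over weaker ones. They also treat strata and baseline as explaining separate variance, although skin status is itself a severity grade. With full overlap, ρ of 0.5–0.6 gives 13–20%.

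Nor is the gain simply free for questionnaire scores, where it might be largest. Their first scheduled value follows randomisation, and recruitment has been running since December 2024, so a pre-randomisation value cannot be recovered for those already enrolled. This part of the objection stands and limits the remedy.

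Finally, the affected analyses are exploratory and unpowered, without p values, and over-wide intervals err on the cautious side. That also stands.

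**Conclusion.** The point holds in a limited form. The stated model omits both randomisation strata and the baseline outcome while calling its differences adjusted. If those variables are prognostic, the 80% and 95% intervals for the exploratory clinical outcomes will be wider than necessary, and conservative because the strata are ignored.

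The size cannot be fixed from the document. Under the assumed values the adjusted 95% interval runs from about the same width (ratio 1.007: weak covariates, 15 sites) to 29% narrower (0.711: ρ 0.6, site ICC 0.10, 5 sites). It is up to 5% wider if the covariates have no prognostic value and sites are many. For PASI the gain is likely to be small because Table 1 limits entry to 2 or less.

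This does not make the estimates biased or invalid: under randomisation the differences remain unbiased. Recruitment, retention, adherence, acceptability and the progression criteria are unaffected.

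**What to change.** In Statistical methods, name the adjustment variables for the comparative models:

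- Clear or nearly clear status, as used for stratification, as a fixed effect.
- Site as a random intercept, or fixed with small sites pooled, to limit the loss of degrees of freedom.
- The baseline value of the outcome where it is measured before randomisation (PASI, Physician and Patient Global Assessment). Either fit post-baseline times only or constrain the baseline means to be equal across arms. For PASI and Physician Global Assessment, month 12 is the only scheduled follow-up, so the first option reduces to an analysis of covariance. Entry criteria leave the two global assessments only two baseline levels, so whichever one defines the stratum need not be entered twice.
- For questionnaires first completed at Training, adjust for strata. Use the Training value only with its post-randomisation timing acknowledged.
- For weeks in disease control and worsening episodes, adjust for strata only.

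If no covariates are intended, the least that is needed is to delete the word adjusted.

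The cost is a few lines of text and no new data. The downside is a few degrees of freedom, and slightly wider intervals (1–5% in the simulation with fixed site terms) if the covariates prove non-prognostic.
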